### Setting

This single-site study takes place at Equip Health. Equip Health provides web-based ED treatment to children and adolescents ages 6-24 years across the United States using an FBT approach.

### Ethical Considerations

This study was reviewed by the Biomedical Research Alliance of New York (BRANY) institutional review board (protocol number 22-016-1096), and it was determined that it does not meet the criteria for human subject’s research as this is a quality improvement study of Equip Health treatment. Thus, institutional review board oversight was not required. Patients or caregivers consented to participate in treatment approach comparison studies upon admission and consented for treatment information to be evaluated and disseminated. Data will be stored in Equip’s Health Insurance Portability and Accountability Act–compliant medical record platform and will be deidentified upon extraction by trained research personnel. Interviews with the RD interventionists will be conducted via a Health Insurance Portability and Accountability Act–compliant Zoom platform. The final study results will be reported in aggregate, and will not contain any personally identifiable information.

### Recruitment

Patients seeking treatment at Equip inquire through Equip’s web-based form through direct email or phone. We randomized 100 eligible patients who enrolled in ED treatment on a rolling basis from May through August 2022.

### Group Assignment

As part of standard of care at Equip Health, all patients receiving FBT are assigned an RD as part of their multidisciplinary treatment team. Upon admission, patients eligible for this study and who consented to be a part of treatment comparison studies at Equip will be randomly assigned using a block design to receive either the calorie-based approach or the Plate-by-Plate approach during renourishment treatment with the RD. Participating patients were randomized for the purpose of having an equal number of participants in each treatment group. All other treatment procedures followed the standard of care for all Equip patients.

### Assessments and Measures

#### Overview

Outcome measures are described below and summarized in Table 1. Additionally, the following demographic data will be extracted from the medical record: age, state of residence, biological sex, gender identity, ED diagnosis, and height. Patients will be followed for up to 12 months, and clinical assessment measures are taken throughout treatment as part of standard practice. However, our primary time point of interest is week 8 of treatment, as this will provide important information about the patient’s response in the early phases of treatment, a critical time period for predicting remission.

**Table 1 table1:** Primary and secondary outcome measures.

Measure		Outcome	Frequency assessed and timepoints of interest
**Primary** **outcome**			
	Weight	Weight change	Twice weekly (baseline, week 8)
**Secondary outcomes**			
	Eating Disorder Examination Questionnaire Short Form	Global total score, Eating concern scale score, Weight concern scale score, and Shape concern scale score	Upon admission, weekly thereafter (baseline and week 8)
	Burden Assessment Scale	Caregiver burnout	Every 40 days (baseline and week 8)
	Parent versus Eating Disorders	Caregiver self-efficacy	Day 14, every 40 days thereafter (baseline and week 8)
	Patient Health Questionnaire	Symptoms of depression	Upon admission, monthly thereafter (baseline and week 8)
	Generalized Anxiety Disorder Scale	Symptoms of anxiety	Upon admission, monthly thereafter (baseline and week 8)
	Clinician semistructured interview	Acceptability and perceived effectiveness of intervention	End of study
	Caregiver semistructured interview	Acceptability and perceived effectiveness of intervention	Treatment week 8 (approximate)

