**Methods:**

Patients (N=100) with either AN or avoidant restrictive food intake disorders (ARFID) aged 6-24 years seeking treatment at a nationwide virtual eating disorder treatment program, were enrolled between May and August 2022. Upon admission, patients were randomly assigned to receive either the calorie-based intervention or Plate-by-Plate approach from their registered dietitian, all of whom have received training as study interventionists. While we were primarily interested in responses during the first 8 weeks of treatment, patients will be followed for up to 12 months. Descriptive statistics were used to describe patient characteristics and demographics. Weight changes and other treatment outcomes between groups will be compared using generalized linear models. Semistructured caregiver and clinician interview transcripts will undergo qualitative analysis.

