This feasibility study will compare the acceptability of 2 digitally delivered dietary interventions and preliminary effectiveness in early stages of treatment: (1) calorie-based meal plans and (2) the Plate-by-Plate approach [24]. Our primary outcome of interest is weight restoration achieved after 8 weeks of treatment, as this is the best predictor of remission. We will also examine the following treatment outcomes by intervention: ED symptoms, anxiety, depression, caregiver burden and self-efficacy, and caregiver’s acceptability and perception of effectiveness. Acceptability and perceived effectiveness will also be measured for clinicians once week 8 outcomes have been captured for all participants. While we are most interested in early treatment response, patients will be followed and clinical outcomes for patients and caregivers reported throughout the entirety of their treatment course as part of standard practice. We anticipate that the findings from this study will help us better understand the needs and experiences of caregivers undergoing FBT and ultimately, whether 1 approach is superior in terms of influence on treatment outcomes. We will also gain insight around commonly held assumptions, such as the running hypothesis that providing caregivers with a calorie target may undermine parental empowerment and self-efficacy. This study will add to existing FBT literature by exploring the impact of dietary interventions that guide caregivers' process for renourishing their child, for which there is currently no research.

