### Procedures

Upon beginning treatment at Equip Health, eligible patients will be randomly assigned to receive either the calorie-based approach or the Plate-by-Plate intervention within their first 1-2 sessions with their assigned RD. In the first phase of treatment, the RD meets exclusively with caregivers (eg, parents or guardians) at a weekly meeting cadence for the first month, and thereafter in accordance with the RD’s judgment.

A high-level summary of each approach is as follows: (1) calorie-based nutrition prescription: following the completion of a nutrition assessment by the RD, caregivers will be prescribed a calorie goal and be instructed to aim to reach that goal daily as a primary focus of treatment. In collaboration with caregivers, a calorie goal will be assigned to 3 meals and 3 snacks daily. For example, the goal may be 3000 kcal per day, comprised of 700 kcal meals 3 times per day, and 300-kcal snacks 3 times per day. Additionally, caregivers are provided 7-day sample menus that align with their calorie prescription. If clinically indicated, they may also receive education on how to increase the caloric density of meals while maintaining low volume. Adjustments will be made throughout the treatment course to calorie prescriptions per RD’s judgment to accommodate the weight restoration goal of 2 lbs per week. During the initial session, caregivers are instructed to send photos and density estimates of all foods consumed by the child to the RD, and feedback will be given speaking to the adequacy of calorie content of meals and snacks in the follow-up sessions. (2) Plate-by-Plate approach is summarized for caregivers in the following steps:

Choose 10-inch platePlate all food groupsFill plateParent decides number of meals or snacksInclude varietyDoes the meal make sense?Final review: Does the plate make sense?

Caregivers are instructed to prompt the patient to complete the plate, and in the case of food refusal, oral supplements are provided to replace the remaining food.

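### The caregiver self-efficacy score that Table 1 calls baseline is taken on day 14, after randomisation and probably after most caregivers have started the assigned approach

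*Protocol article*

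**What the plan says.** In Table 1 of the protocol article, the row for the Parent versus Eating Disorders scale (caregiver self-efficacy) reads "Day 14, every 40 days thereafter (baseline and week 8"). The late start is not general. The eating disorder symptom questionnaire in the same table is listed as "Upon admission, weekly thereafter (baseline and week 8"), and the depression and anxiety scales also begin at admission.

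Randomisation comes earlier. Methods, Group Assignment states: "Upon admission, patients eligible for this study and who consented to be a part of treatment comparison studies at Equip will be randomly assigned". Methods, Procedures places assignment "within their first 1-2 sessions with their assigned RD". It adds that in the first phase the dietitian sees caregivers only, "at a weekly meeting cadence for the first month". In the calorie arm, tasks begin at once: "During the initial session, caregivers are instructed to send photos and density estimates of all foods consumed by the child to the RD".

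The measure bears on a stated question. The end of the Introduction names caregiver self-efficacy as an outcome and cites the hypothesis that "providing caregivers with a calorie target may undermine parental empowerment and self-efficacy".

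On analysis, the abstract's Methods paragraph says only: "Weight changes and other treatment outcomes between groups will be compared using generalized linear models". The Statistical Analysis section specifies a model for the rate of weight change and names none for this scale.

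**The concern.** A baseline should be measured before the treatment can have affected it. The day-14 score comes after randomisation. The caregivers who complete the scale are also the people who receive the dietitian's guidance, so for many of them it probably comes after the first contact with the assigned approach. It is then an early outcome carrying a baseline label.

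The label invites one of two uses: a change score from day 14 to week 8, or a week-8 comparison adjusted for day 14. Both condition the comparison on something the approach may already have moved. A calorie target that unsettled caregivers in the first two weeks would have that early effect partly or wholly removed from the contrast. This is one of the assumptions the trial sets out to test, so a small difference between arms on this scale could be over-read.

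**Working it through.** The protocol gives no effect size, power or sample-size figure for this scale, so there is nothing to reproduce. The check uses the schedule first and then illustrative accrual paths.

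**Schedule (Table 1).** Scores fall on days 14, 14 + 40 = 54, 94 and so on. Week 8 is day 8 × 7 = 56, so day 54 is the week-8 value. The interval from the so-called baseline to week 8 is 40 days, and 14/56 = 25% of the eight-week window lies before it. That day 14 counts from admission is inferred from the neighbouring rows.

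**Exposure before day 14 (Procedures).** Let the first dietitian session fall on day s, with weekly sessions after it. Exposure is 14 − s days if the approach starts at session 1, and 14 − (s + 7) days if it starts at session 2.

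| First session | Sessions on or before day 14 | Exposure, start at session 1 | Exposure, start at session 2 |
|---|---|---|---|
| day 0 | 3 | 14 days | 7 days |
| day 3 | 2 | 11 days | 4 days |
| day 7 | 2 | 7 days | none |
| day 14 | 1 | none | none |

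A caregiver is unexposed on day 14 only if the first session is on about day 14 or later, or if the approach starts at session 2 and the first session is on day 7 or later.

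**What the contrast estimates.** Let D(t) be the between-arm difference on day t. A change score estimates D(54) − D(14). With equal variances and correlation r between the two scores, covariate adjustment estimates D(54) − r·D(14). A comparison of day-54 scores estimates D(54).

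**Share of D(54) captured by a change score.** The accrual paths are assumed: linear, or exponential with a 14-day half-life.

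- Onset day 0, linear: 40/54 = 74%.
- Onset day 0, half-life: D(54) ∝ 1 − 2^(−54/14) = 0.931 and D(14) ∝ 0.5, so (0.931 − 0.5)/0.931 = 46%.
- Onset day 7, linear: 40/47 = 85%.
- Onset day 7, half-life: D(54) ∝ 1 − 2^(−47/14) = 0.902 and D(14) ∝ 1 − 2^(−7/14) = 0.293, so (0.902 − 0.293)/0.902 = 68%.
- Onset day 14: D(14) = 0, so 100%.

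**Illustration with the enrolled numbers.** Take 50 per arm (Results, Demographics), two-sided 5%, an assumed D(54) of 0.5 SD, r = 0.5, and a fraction f of D(54) already present on day 14. The change-score difference is 0.5(1 − f), with SD √(2(1 − 0.5)) = 1. The adjusted difference is 0.5(1 − 0.5f), with residual SD √(1 − 0.25) = 0.87.

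| f | Change-score difference (power) | Adjusted difference (power) |
|---|---|---|
| 0 | 0.50 SD (0.71) | 0.50 SD (0.82) |
| 0.25 | 0.375 SD (0.47) | 0.44 SD (0.71) |
| 0.50 | 0.25 SD (0.24) | 0.375 SD (0.58) |

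The day-54 comparison alone keeps 0.50 SD at every f. Its SD is 1, the same as the change score's at r = 0.5, so its power is 0.71 throughout.

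**The case against.** The strongest reply is that the article states no change score and no baseline covariate for this scale. It promises only a generalized linear model comparison between groups, and the detail may sit in an analysis plan that is not shown. A week-8 comparison, which is the remedy, is not excluded. This stands. A reader might infer that a stated analysis is biased, but the documents do not support that. They do fix the day and the label, and the label points to the two uses that cause harm.

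Second, exposure by day 14 is inferred, because neither the first session day nor the origin of day 14 is given. This also stands, so the claim is limited to most caregivers, probably.

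Third, a reader might attach a fixed cost to the problem. With onset on day 0, the captured shares of 74% and 46% imply 1/0.741² = 1.8 and 1/0.463² = 4.7 times the sample for equal power. Onset on day 7 lowers these to about 1.4 and 2.2, and onset on day 14 removes the loss. No single factor can be defended, and these apply only to a change score.

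Fourth, a reader might infer that the bias always runs toward no difference, so that the self-efficacy hypothesis would be wrongly dismissed. That requires a difference that builds in one direction through day 54. If an early difference fades so that D(14) exceeds D(54), the change score takes the opposite sign. The caregiver interviews also give separate evidence on experience with the assigned approach.

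Finally, adjusting for day 14 need not lose power. At f = 0.25 it matches the unadjusted comparison in the illustration (0.71), and at smaller f it does better. The objection to it is that it no longer estimates the whole effect of assignment.

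**Conclusion.** The point holds in conditional form. The score labelled baseline follows randomisation and, for most caregivers, probably follows the start of the assigned approach. Used as its label invites, it removes from the self-efficacy contrast all (change score) or part (covariate adjustment) of any difference present on day 14. Where the effect builds in one direction, the contrast is pulled toward no difference.

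The size cannot be determined from the protocol. The captured shares of 46% to 100% rest on assumed onset days and accrual shapes, and if no difference has emerged by day 14 nothing is lost. The power figures also rest on an assumed 0.5 SD effect and a correlation of 0.5.

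The scope is one secondary outcome in a feasibility trial. The primary weight outcome runs from admission and is unaffected.

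**What to change.** - In Table 1, relabel the day-14 score as an early post-randomisation outcome and report it by arm as such.
- State that the week-8 comparison uses the day-54 score, without subtracting or adjusting for day 14.
- Adjust only for variables known before randomisation. Age, sex and diagnosis are already extracted from the medical record (Assessments and Measures, Overview). The caregiver burden scale is not a safe choice, because Table 1 gives it a 40-day interval and no admission time.
- State as a limitation that no pre-assignment self-efficacy score exists. All 100 patients are enrolled, so it cannot now be collected.

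The change is to wording and analysis only. The cost is the precision a true baseline would have given: in the illustration, power of 0.71 instead of 0.82, before any gain from age, sex and diagnosis.

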**Objective:**

Our objective is to compare the effectiveness and acceptability of 2 digitally delivered dietary interventions frequently used in eating disorder treatment settings: (1) calorie-based meal plans and (2) the Plate-by-Plate approach. Specifically, we will explore any potential differences in weight restoration achieved over 8 weeks of treatment as a primary measure of effectiveness, as well as additional treatment outcomes (ED symptoms, anxiety, depression, caregiver burden, and perceived effectiveness and acceptability for both caregivers and clinicians).

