#### Caregiver Semistructured Interviews

A semistructured interview (Multimedia Appendix 2) will be completed with caregivers to assess their experience with the assigned renourishment strategy. Caregivers will be contacted directly by a member of the research team via their preferred email address to schedule and the interviews will be conducted via phone. If the caregiver does not respond to contact efforts, a Health Insurance Portability and Accountability Act–compliant Google Forms link will be provided via preferred email through which the caregiver can answer the interview questions, after which efforts to reach the caregiver will be discontinued.

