### Training and Fidelity

All Equip RDs have experience in treating EDs using a variety of dietary interventions within and outside of the FBT framework. Upon hiring, Equip RDs complete an in-depth video training on various interventions commonly used in ED treatment, including the Plate-by-Plate approach and calorie-based meal plans. RD interventionists undergo a live training session overviewing study protocols and each intervention, and a prerecorded training on the Plate-by-Plate intervention (led by authors of the Plate-by-Plate intervention). Interventionists will receive ongoing training as needed and supervision to ensure adherence to the respective approaches and will additionally be trained to notify research staff of any fidelity issues or protocol deviations by other providers on a treatment team.

Electronic records will be reviewed by study personnel on a weekly basis to ensure adherence to the assigned treatment approach. Specifically, session documentation, chat communications, and any document exchanges will be reviewed. Any fidelity issues (and the subsequent potential need for participant withdrawal) will be discussed by research personnel and interventionists. Further, should a patient discharge prior to week 8 of treatment, or if the RD determines that the assigned intervention is a poor fit for the patient, the patient may be withdrawn.

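### Caregiver acceptability is assessed once, at about treatment week 8, with no assessment described for caregivers of patients discharged or withdrawn before then, so negative views can be under-sampled

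*Protocol article*

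**What the plan says.** The Objective in the Abstract is to "compare the effectiveness and acceptability of 2 digitally delivered dietary interventions", and the end of the Introduction repeats acceptability as an aim of the feasibility study. In Table 1 the caregiver semistructured interview is the only measure of how caregivers themselves judge the approach. Its row gives one outcome and one timepoint: "Acceptability and perceived effectiveness of intervention Treatment week 8 (approximate").

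Caregiver Semistructured Interviews says that the interview "will be completed with caregivers to assess their experience with the assigned renourishment strategy". Caregivers are contacted by email and interviewed by phone. Those who do not respond are offered a written alternative: a "Google Forms link will be provided via preferred email through which the caregiver can answer the interview questions". Contact attempts then stop. The section does not say whether families who have been discharged or withdrawn are approached.

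Training and Fidelity names two routes out of the study that can come before the interview. One is early discharge: "should a patient discharge prior to week 8 of treatment". The other is a judgement by the dietitian: "if the RD determines that the assigned intervention is a poor fit for the patient, the patient may be withdrawn". The same section allows for withdrawal over fidelity issues. Strengths and Limitations adds a case-by-case decision on withdrawal where caregivers cannot be oriented to the assigned approach.

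**The concern.** The interview is set on a treatment clock, and a patient discharged at week 4 has no treatment week 8. A patient withdrawn from the study may remain in care, but nothing says that the caregiver is still interviewed. Two of the foreseen reasons for withdrawal, poor fit and failed orientation, come close to being acceptability failures themselves. The loss before the only caregiver assessment could therefore be related to the outcome rather than incidental.

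If those caregivers are missed, the interviews describe acceptability among families for whom the approach was at least workable. The strongest objections may be absent from the themes. If one approach loses more families, or loses more dissatisfied ones, the two arms can look alike when they are not, or different when they are alike. This matters because the Significance section expects the study to identify a preferred approach. Keeping every patient's weight in the primary analysis would not recover these views.

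**Working it through.** The article states no attrition rate, acceptability rate or acceptability score, so there is no figure to reproduce. The check has two parts: what the schedule covers, and how far selection could move a simple summary.

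**Coverage under the text as written**

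- Patient completes eight weeks: caregiver interview due.
- Family stops using the approach but stays in treatment and in the study: week 8 is still reached, interview due.
- Patient discharged before week 8: no treatment week 8, and no exit assessment described.
- Patient withdrawn for poor fit, fidelity or failed orientation: not stated either way.

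The other measures do not fill the last two cells. The dietitian interview records clinicians' views. The burden and self-efficacy scales measure other constructs. The online form is a fallback for non-response to scheduling, not an exit assessment.

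**Illustrative size (all rates assumed)**

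Let *d* be the share of an arm lost before interview and never asked, *s* the proportion of interviewed caregivers who find the approach acceptable, and *q* that proportion among those lost.

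- Acceptability in the whole arm = (1 − d)·s + d·q
- Overstatement = s − [(1 − d)·s + d·q] = d·(s − q)

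With s = 80% and 50 patients per arm (Demographics), the overstatement in percentage points is:

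| q | d = 10% (45 interviewed) | d = 20% (40) | d = 30% (35) |
|---|---|---|---|
| 0% | 8 | 16 | 24 |
| 20% | 6 | 12 | 18 |
| 40% | 4 | 8 | 12 |
| 80% | 0 | 0 | 0 |

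Three between-arm cases:

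1. *Unequal loss, equal views among those interviewed.* With s = 80%, q = 20% and losses of 10% and 30%, whole-arm acceptability is 0.90 × 0.80 + 0.10 × 0.20 = 74% and 0.70 × 0.80 + 0.30 × 0.20 = 62%. The interviews show 80% in both arms, and a 12-point difference is hidden.
2. *Unequal loss, equal acceptability in the whole arms.* With 70% in each arm, q = 20% and losses of 10% and 20%, the interviews show (0.70 − 0.10 × 0.20)/0.90 = 75.6% and (0.70 − 0.20 × 0.20)/0.80 = 82.5%. A false difference of 6.9 points favours the arm that lost more families.
3. *Equal loss, different views among those lost.* With d = 20% and s = 80% in both arms, and q = 20% in one and 40% in the other, the overstatements are 0.20 × 0.60 = 12 and 0.20 × 0.40 = 8 points. A 4-point difference is hidden.

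With equal *d*, *s* and *q* in both arms, each level is overstated equally and the comparison is not biased.

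**The case against.** A reader might infer that caregivers who leave early or give up the approach are never asked, and that acceptability is therefore overstated in the arm that loses more families. The article does not support that.

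- Withdrawal is discretionary, and the interview section does not restrict contact to families still enrolled. Email, phone and the online form need no continuing sessions. A family that drops the approach but stays in treatment is still due an interview.
- Whether withdrawn families are followed up is an operational detail that a journal article may leave to the full protocol.
- Bias in the level needs lost caregivers to be both unasked and less satisfied. Distortion of the comparison needs, in addition, a difference between arms in losses or in the views of those lost. The article gives no rates for any of this.
- The transcripts are to be analysed qualitatively, and no acceptability score or cut-off is defined. A difference in percentage points is a way to see the mechanism, not a quantity that the trial plans to estimate.
- Dietitians, who judge fit and report orientation problems, are interviewed, and records are reviewed weekly, so failures of an approach are not invisible.

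Most of this stands and limits the claim to a risk. It does not dispose of it. The single timepoint is stated in Table 1, not left open. The reasons for earlier withdrawal are stated too, and they bear on the outcome. Clinicians' accounts do not replace the caregivers' own.

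**Conclusion.** The point holds as a conditional risk. The stated schedule can miss caregivers of patients discharged or withdrawn before week 8, so negative views can be under-sampled and acceptability overstated. The comparison between approaches is distorted if early losses, or the views of those lost, differ by arm.

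The size is unknown. Under assumed losses of 10% to 30%, with 80% acceptability among those interviewed and 0% to 40% among those lost, the overstatement runs from 4 to 24 points. It is zero if nobody is lost, if those lost are interviewed, or if their views match the others'. For the planned qualitative analysis, the equivalent harm is missing or thin negative themes, possibly unevenly by arm.

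The weight outcome is not affected by this point. It merits a change because acceptability is a named objective and the remedy is small.

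**What to change.** - In Table 1, set the caregiver interview at treatment week 8 or shortly after discharge or study withdrawal, whichever comes first, with the same script and the same online-form fallback. State the same rule under Caregiver Semistructured Interviews.
- Enrollment closed in August 2022 and data collection was expected to finish by November 2022, so the new timepoint may come too late for many families. Where a family has already left without being asked, send the form retrospectively. Flag those replies, because recall is longer and the mode differs from a phone interview, and read the themes with and without them.
- Report by assigned arm the numbers interviewed, reached by form, not reached, and lost before week 8, with reasons. If leavers were in fact interviewed, say so.

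The cost is a line in Table 1, a sentence in the text and a small number of extra emails or calls. The downside is that some interviews will reflect shorter exposure to the approach and some leavers will not reply. The change concerns only when caregivers are asked and does not touch treatment.
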